### 2.14. Statistical Methods

This study is a phase II trial primarily focused on the effects of Bifidobacterium and perilla oil when taken properly. Therefore, the main analysis will be performed in a per protocol set (PPS), which is defined as participants who complete the final post-intervention primary outcome assessment and complete the protocol-specified interventions. Completion of the protocol-specified interventions is defined as completion of least 4 of the 12 weeks of Bifidobacterium and perilla oil administration; these participants will be considered to have completed the protocol-specified interventions based on a meta-analysis of probiotic interventions for anxiety symptoms where the minimum treatment period in studies demonstrating efficacy was 4 weeks [45].

In the secondary analysis, analysis will be performed on all randomized cases based on the intention-to-treat (ITT) principle, and discrepancies in the analysis using the PPS will also be examined. Regarding patient background, summary statistics (mean, standard deviation, and frequency) will be calculated based on the characteristics of the items, and the presence or absence of bias in the three baseline groups in each item will be evaluated based on analysis of variance or the chi-squared test.

The objective of the primary analysis of this study is to collect data to inform a main confirmatory clinical trial (phase III). Regarding the primary outcome, the primary hypothesis is that the mean CARS scores of the intervention groups (Bifidobacterium alone or Bifidobacterium plus perilla oil) at week 12 will be significantly lower than those of the control group. The intervention will be considered effective if the null hypothesis is rejected. The difference in the mean CARS score at 12 weeks after random allocation between the intervention groups and the control group will be analyzed using the unpaired t-test. In the primary analysis, we will not compare the effects between the two intervention groups. Missing values or modeling will not be imputed for primary analysis. Sensitivity analyses will be performed for the primary outcome after imputing missing data using the multiple imputation method.

The following secondary and sensitivity analyses will be performed for additional discussion of the primary analysis, which will determine the need for further studies. These analyses will be conducted after the primary analysis is completed. For all continuous outcomes (CARS, PHQ-9, IBS-SI, and gut microbiome composition), differences in the scores at 12 weeks and changes between baseline and 12 weeks will be examined using non-paired t-tests and mixed-effect models for repeated measures analysis using repeated timepoints and age, disease duration, and hospital as covariates. For dichotomous or dichotomized categorical outcomes such as ARs and proportion of participants with a moderate or high level of FCR at 12 weeks, relative risk will be calculated. Chi-squared and Fisher’s exact tests will be used for statistical significance testing. The aforementioned analyses will be performed between the combined intervention group (those treated with Bifidobacterium alone and those treated with Bifidobacterium plus perilla oil; *n* = 30) and the control group (*n* = 15). The purpose of this analysis is to increase the power of the hypothesis test to examine whether Bifidobacterium intervention is effective against FCR. This is a supplemental analysis to reinforce the arguments of the primary analysis. Furthermore, to explore the association of changes in symptoms with the gut microbiome and PUFAs, we will perform correlation analyses.

This study will not include an interim analysis. If either of the intervention groups (Bifidobacterium alone and Bifidobacterium plus perilla oil) are inferior to the usual treatment group (control group), it is not a matter of concern whether it is statistically significant or not, so the test will be one-sided. The significance level of the entire test is 2.5% for one side. While this decision might lead to errors in multiple tests, this will be the first study of nutritional intervention for FCR. Therefore, we consider the avoidance of beta errors to be preferable over alpha errors. However, 95% confidence intervals will be presented for differences among groups.

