## 2. Methods and Analysis

### 2.1. Study Design

This study has been planned as an exploratory clinical study (phase 2) and will be conducted as a three-arm, 12-week parallel group, masked-rater randomized controlled trial (RCT). The study is registered in the Japan Registry of Clinical Trials (jRCT; Trial ID jRCTs031200029). Participants will be randomized with 1:1:1 allocation to receive Bifidobacterium plus perilla oil, Bifidobacterium alone, or no intervention (control). A total of 15 participants will be allocated to each arm. These interventions will end within 12 weeks of the registration of each participant. The primary outcome will be FCR severity at 12 weeks as assessed by masked raters using the 4-item Concerns about Recurrence Scale (CARS) that asks about overall fear of recurrence.

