### 2.9. Data Collection Methods

The following information will be collected at the baseline assessment: age, sex, marital status, cancer stage, surgical history, history of radiation therapy, work status, family status, medication history (mental illness, other disease, antibiotic use, psychotropic drugs), body height/weight, and diet assessed using the Food Frequency Questionnaire (FFQ) [38,39]. For baseline characteristics, information will be collected from medical records as well as from the individual participants through questionnaires and interviews. We will also assess blood fatty acids at baseline with a custom test kit (Xerion Pharmaceuticals, Victoria, Australia) using dried blood spot testing as described previously [19]. All participants will receive a gift voucher for 2000 JPY (approximately 18 USD) for their participation after each assessment. An overview of the schedule for the assessments is shown in Table 1.

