### 2.13. Sample Size Calculation

The sample size was estimated based on power analysis using the CARS score. To our knowledge, no previous reports have examined the effects of nutritional interventions on FCR, so there is no reference on which we can base our power calculation.

In our observational study conducted between 2017 and 2018, the mean CARS score of a subset of breast cancer survivors who met the eligibility criteria for this study with a prior history of chemotherapy and CARS score ≥3 was 3.96 (SD ± 0.67). Furthermore, in this study, the intervention will be considered clinically significant if the mean CARS score at week 12 in the intervention group is 1 point lower than the mean CARS score at week 12 in the control group. The CARS score ranges from 1 (not worried at all) to 6 (always very worried). In the opinion of breast surgery specialists (TK and AM), a 1-point decrease in this score from 4 (somewhat worried) to 3 (slightly worried) is clinically significant.

Thus, based on the above hypothesis and the results of our previous study, the mean difference in CARS scores was estimated to be 1.0 ± 0.67 (SD) between the Bifidobacterium plus perilla oil group and the control group and between the Bifidobacterium and the control groups at 12 weeks after random allocation. To detect the difference between the two groups, using unpaired *t*-tests with a one-sided alpha of 2.5% and power of 90%, the calculation showed that 11 participants per group would be required in the analysis population. This was calculated using G*Power software (ver.3.1.9.4). Assuming 4 dropouts per group, 15 participants will be enrolled per group (45 in total).

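### Baseline ANOVA and chi-squared tests cannot establish whether the three arms are biased: a significant item is chance, and a non-significant one shows little at 11 to 15 per arm

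*Protocol article*

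**What the plan says.** In the protocol article, section 2.14 (Statistical Methods) treats patient background in one sentence with two parts. The first is descriptive: "summary statistics (mean, standard deviation, and frequency) will be calculated based on the characteristics of the items". The second is inferential: "the presence or absence of bias in the three baseline groups in each item will be evaluated based on analysis of variance or the chi-squared" method. The question these tests are meant to answer is "the presence or absence of bias in the three baseline groups in each item". No significance level is given for them, and no size of imbalance is named as important.

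The items come mainly from section 2.9: "The following information will be collected at the baseline assessment: age, sex, marital status, cancer stage, surgical history, history of radiation therapy", followed by work and family status, four kinds of medication history, height and weight, diet by questionnaire, and blood fatty acids.

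The numbers available are set in sections 2.1 and 2.13: "Participants will be randomized with 1:1:1 allocation", "the calculation showed that 11 participants per group would be required in the analysis population", and "Assuming 4 dropouts per group, 15 participants will be enrolled per group (45 in total").

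**The concern.** The sentence makes a significance test the means of deciding whether bias is present or absent. Neither outcome of the test supports that conclusion.

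- **A significant item.** Among all randomised participants the null hypothesis, that the arms are drawn from one population, is true by design. A small p-value there is a chance event, and when many items are tested some will be significant.
- **A non-significant item.** With 11 to 15 per arm the tests have little power against moderate imbalances, so failure to reject says little about comparability.

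How far an imbalance distorts the week-12 CARS comparison depends on its size and on how strongly the item predicts week-12 CARS. The p-value measures neither. At stake is the truth of what the trial report will say about the comparability of its arms.

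**Working it through.** **Inputs from the protocol article.** Three arms, 1:1:1 (2.1). 15 enrolled and 11 analysed per arm; CARS SD 0.67; target difference 1.0 point (2.13). ANOVA or chi-squared for each item (2.14).

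**Assumptions.** Two-sided 5% level for the baseline tests. A relevant imbalance is taken as 0.5 SD or 20 percentage points, with other sizes shown. Items are treated as independent when counting false alarms.

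**Step 1: the plan's own figure.** For a two-group t-test with d = 1.0/0.67 = 1.49 and one-sided alpha 2.5%, the noncentral t distribution gives power 88.4% at 10 per group and 91.4% at 11. The stated 11 for 90% power is reproduced, and 11 + 4 = 15.

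**Step 2: chance of a false alarm.** Section 2.9 gives eight single items from age to family status, four medication histories, height and weight: 8 + 4 + 2 = 14. Diet and blood fatty acids bring this to 16 if each counts once and 18 if each counts twice. The chance of at least one significant item in a correctly randomised trial is 1 − 0.95^k:

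| Items k | Chance of at least one |
|---|---|
| 14 | 51% |
| 16 | 56% |
| 18 | 60% |

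**Step 3: miss rate of the ANOVA.** Let one arm differ by d SD from two equal arms. The noncentrality is n × d² × 2/3, with 2 and 3n − 3 degrees of freedom. At d = 0.5 it is 11 × 0.25 × 2/3 = 1.83 and 15 × 0.25 × 2/3 = 2.50. The critical F is 3.316 (n = 11) and 3.220 (n = 15).

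| True gap, one arm off | Missed, n = 15 | Missed, n = 11 |
|---|---|---|
| 0.5 SD | 74% | 81% |
| 0.8 SD | 42% | 56% |
| 1.0 SD | 22% | 37% |
| 1.49 SD (1 CARS point) | 1% | 6% |

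On the CARS scale, 0.5 SD is 0.5 × 0.67 = 0.34 points, about a third of the 1-point target.

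**Step 4: observed gap needed for significance.** With one arm apart from two equal arms, F = n × g²/3 for an observed gap g in SD units, so g = √(3 × Fcrit/n). This gives √(3 × 3.316/11) = 0.95 SD and √(3 × 3.220/15) = 0.80 SD.

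**Step 5: miss rate of chi-squared.** Full enumeration of the 3 × 2 table at 30%, 30% and 50% gives power 15.8% (n = 11) and 20.1% (n = 15), so 84% and 80% are missed. At 30%, 30% and 70% the miss rates fall to 49% and 36%.

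**The case against.** The strongest reply is that nothing hangs on these tests. The primary analysis is fixed as an unpaired t-test in the per-protocol set, and the mixed-model covariates (age, disease duration, hospital) are named in advance. No covariate, analysis set or conclusion is chosen by a baseline p-value. This stands, and it limits the weight of the point.

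Second, the same sentence already promises means, standard deviations and frequencies, so a reader will be able to see the size of each imbalance. This stands too. What remains wrong is that the plan draws its conclusion about bias from the tests.

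Third, the miss rates depend on what counts as relevant, which the protocol does not define. This is correct. A statement that the tests miss three quarters or more of imbalances holds near 0.5 SD or 20 points, not at 0.8 SD and above. The false-alarm figures likewise depend on the item count and on independence.

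Two stronger readings are tempting, and the document supports neither.

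- **Raised false-positive risk.** A reader might infer that clearing a baseline CARS gap this way raises the false-positive rate of the primary comparison. Given a chance gap favouring the intervention, an unadjusted t-test does reject too often, but that comes from the lack of adjustment. Over all randomisations the error of each comparison stays at 2.5%, and removing the baseline tests would not change it.
- **A check on the per-protocol set.** A reader might infer that the tests are the plan's safeguard for that set. Section 2.14 does not say in which set they are run. It handles departures from randomisation separately, through an analysis of all randomised cases with discrepancies examined, and through multiple imputation as a sensitivity analysis.

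**Conclusion.** The point holds as a defect in a stated inference. In the randomised set, a significant item does not show bias. At 11 to 15 per arm, a non-significant item does not exclude an imbalance of moderate size. The miss rates of 74% to 81% (ANOVA, 0.5 SD) and 80% to 84% (chi-squared, 30/30/50%) rest on the assumed 5% level and on those imbalances being the relevant ones. The 51% to 60% chance of a false alarm rests on 14 to 18 independent items.

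The consequence is a possible false statement about comparability in the report. No analysis decision and no type I error rate is affected. The weight is minor.

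**What to change.** In section 2.14, delete the evaluation of baseline bias by ANOVA and chi-squared. Keep the planned summary statistics and present them by arm for all randomised participants and for the per-protocol set. Add the standardised difference of each intervention arm from control. State that imbalance will be judged by its size and by the item's expected relation to week-12 CARS.

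Do not attach a pass/fail cut-off to the standardised differences. In simulated, correctly randomised trials of this size, a limit such as 0.25 is exceeded in at least one of the two control comparisons about 72% (n = 15) to 78% (n = 11) of the time per continuous item, so it would create more false alarms than the tests it replaces.

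The cost is a changed sentence and a changed column in the baseline table. No new data or participants are needed, and the only loss is the column of baseline p-values.

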### 2.5. Randomization and Masking

After completing the baseline assessment, participants will be randomly assigned at a of 1:1:1 allocation ratio to one of the three groups: the Bifidobacterium plus perilla oil group, the Bifidobacterium group, or the control group. Within the Hope eACReSS electronic data capture system (EDC) system, made available by the University Hospital Clinical Trail Alliance (http://plaza.umin.ac.jp/~UHCTA/edc.html, accessed on 5 July 2021), randomization will be performed using a minimization method and will be balanced using the following two factors: stratification age (<65 years, ≥65 years) and duration from diagnosis (<5 years, ≥5 years).

The primary outcome will be evaluated by the CRC and masked raters. At baseline, the CRC will evaluate the outcome before allocation. At 12 weeks, raters masked to all information regarding the allocation of this study will evaluate this outcome over the phone. The primary investigator (RO) will hold a workshop on the primary outcome evaluation for the CRC and masked raters using simulated recordings to confirm the evaluation method and will assess the inter-rater reliability for score evaluation. The primary outcome, FCR, is a subjective concept and result, and the CARS used in the evaluation is a self-reported scale, but in order to standardize the conditions of the responses, a masked rater will read the questionnaire aloud and will spend 5 min conducting the evaluation. This procedure is based on previous studies in which the primary outcome was a self-reported measure evaluated by masked raters [34,35].

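### The deciding test is an unadjusted t-test of week-12 CARS that leaves out the pre-allocation CARS score; it is valid, but gives up precision and lets chance baseline imbalance into the effect estimate

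*Protocol article*

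**What the plan says.** Section 2.14 makes the comparison of week-12 CARS means the deciding analysis: the difference "between the intervention groups and the control group will be analyzed using the unpaired t-test". An intervention counts as effective if that null hypothesis is rejected. No covariate is named, and the analysis set is the per protocol set.

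Section 2.5 shows what is known before allocation. On the primary measure, "At baseline, the CRC will evaluate the outcome before allocation". On allocation, "randomization will be performed using a minimization method and will be balanced using the following two factors": age (below 65, or 65 and over) and time since diagnosis (below 5 years, or 5 and over). Baseline CARS is not among them.

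Baseline information and adjustment appear later in Section 2.14, among analyses to be run once the primary one is complete. These are t-tests on change from baseline to week 12, and "mixed-effect models for repeated measures analysis using repeated timepoints and age, disease duration, and hospital as covariates". Baseline balance is to be examined by analysis of variance or chi-squared tests, but the result has no stated role in the primary analysis.

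Section 2.13 sizes the trial for the unpaired t-test at one-sided 2.5% and 90% power, and concludes that "11 participants per group would be required in the analysis population".

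**The concern.** A baseline score on the outcome scale is usually informative about the later score. Here it is collected at no extra cost and then left out of the test that decides the trial. Two things follow if baseline and week-12 CARS are correlated.

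- Variation between patients that the baseline could explain stays in the error term, so the confidence interval is wider than it need be.
- With about 11 per arm, chance differences in baseline CARS are not small, and nothing in the allocation scheme limits them. Part of any such difference appears in the unadjusted estimate as if it were treatment effect.

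Both matter because the stated aim is to estimate efficacy and effect size for a phase III trial, and because Section 2.14 says that missing a real effect is the error the investigators most want to avoid. The per protocol set adds a further reason: exclusions after randomisation can create baseline differences that are not due to chance.

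**Working it through.** **Inputs.** From Section 2.13: difference 1.0, SD 0.67, one-sided alpha 0.025, 11 analysed per arm. The SD is cross-sectional, from an observational subset: "CARS score ≥3 was 3.96 (SD ± 0.67"). The correlation r between baseline and week-12 CARS is not in the article; it is assumed here over 0 to 0.7.

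**1. The plan's own figure.** Standard error of a difference in means = 0.67 × √(2/11) = 0.286. Noncentrality = 1.0 / 0.286 = 3.50 on 20 df. Power from the noncentral t is 0.914 at 11 per arm and 0.884 at 10, so 11 is the smallest adequate size. The stated figure reproduces.

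**2. Chance baseline imbalance.** With the same SD at baseline, the standard error of a baseline CARS difference between two arms is also 0.286, so its 95% range is ±1.96 × 0.286 = ±0.56 points. The chance of a difference above 0.3 points in either direction is about 0.29; above 0.5 points, about 0.08.

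**3. Carry-over.** With equal SDs at the two times, the expected carry-over into the unadjusted difference is r × imbalance. At r = 0.5, a 0.3-point imbalance moves the estimate by 0.5 × 0.3 = 0.15 points. Simulation at r = 0.5 and 11 per arm:

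| | t-test | ANCOVA on baseline |
|---|---|---|
| Type I error, overall | 0.025 | 0.025 |
| Type I error, given about 0.3 points in favour of the active arm | 0.046 | 0.025 |
| Power for 1.0 point, given about 0.3 points against the active arm | 0.835 | 0.960 |

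**4. Power with a single three-arm ANCOVA.** Covariates are baseline CARS and the two minimisation factors. With 33 analysed, error df = 33 − 3 − 3 = 27, against 20 for the pairwise t-test. Simulated at SD 0.67 and a 1.0-point difference, with the two factors balanced across arms and not prognostic, and a common variance:

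| r | three-arm ANCOVA | t-test |
|---|---|---|
| 0 | 0.91 | 0.91 |
| 0.2 | 0.92 | 0.91 |
| 0.3 | 0.93 to 0.94 | 0.91 |
| 0.5 | 0.97 | 0.91 |
| 0.7 | above 0.99 | 0.91 |

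Type I error stayed at about 0.025. Part of the gain at low r comes from pooling the error variance over three arms rather than from the covariates: with no covariate, noncentrality 3.50 on 33 − 3 = 30 df already gives 0.923.

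**5. Power with separate two-arm fits.** For baseline CARS alone, the variance relative to the t-test is (1 − r²) × (1 + 1/18), where 18 = 2 × 11 − 4. It equals 1 at r = √(1 − 18/19) = 0.23, so adjustment loses slightly below that. For all three covariates the multiplier is 1 + 3/16 on 17 df, which gives no credit for balance on the factors.

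| r | baseline only | baseline + two factors | t-test |
|---|---|---|---|
| 0 | 0.898 | 0.857 | 0.914 |
| 0.3 | 0.923 | 0.887 | 0.914 |
| 0.4 | 0.941 | 0.910 | 0.914 |
| 0.5 | 0.962 | 0.937 | 0.914 |
| 0.7 | 0.995 | 0.988 | 0.914 |

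If minimisation balances the factors well, the three-covariate losses are smaller and the fit is roughly level with the t-test at r = 0.3. Either way, pairwise fitting with three covariates brings no worthwhile gain at r of about 0.3 or below.

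**The case against.** The strongest reply is that the unpaired t-test is a valid, simple test, consistent with the sample-size calculation, in a trial that calls itself exploratory. All of that stands. Several stronger readings should therefore be set aside.

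- A reader might infer that the primary test has an inflated false-positive rate. It does not. Overall type I error is nominal; the 0.046 above is conditional on one direction of imbalance and is offset by the other.
- A reader might infer that leaving out the minimisation factors makes the standard error too small. The tendency is the reverse: if those factors are prognostic, omitting them tends to make the t-test conservative. If they are not, little is lost.
- A reader might infer that the sample size is wrong. It is right for the test named.
- A reader might infer that baseline CARS is the strongest predictor of week-12 CARS. The article gives no correlation. Selection on at least 3 points on the intensity item, and the change from the coordinator at baseline to masked telephone raters at week 12, could both lower it.
- A reader might infer that the plan never uses the baseline. It does, in the secondary change-from-baseline tests and possibly through the repeated timepoints of the mixed model. So estimates that use it will exist, but they do not decide the primary result.

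What survives is narrower: a covariate measured before allocation is excluded from the deciding test, where it could only help or cost very little.

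**Conclusion.** The point holds as a matter of efficiency and of protection against chance imbalance, and the change is worth making. At the protocol's own SD, a three-arm ANCOVA costs essentially nothing at r = 0, adds about 2 to 3 points of power at r = 0.3, about 6 at 0.5 and about 8 at 0.7. Since power for 1.0 point is already 0.91, the larger benefit is to the estimate: baseline differences of 0.3 points or more are expected in roughly 3 comparisons in 10, and ANCOVA removes their expected carry-over.

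This rests on an assumed r, on SD 0.67 holding at both times, on 11 analysed per arm, and on a common variance across arms. That the primary test is unadjusted is certain; the size of the gain is not.

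**What to change.** In Section 2.14, replace the primary unpaired t-test by one three-arm ANCOVA of week-12 CARS on arm, with baseline CARS as the key covariate and the two minimisation factors (age group, time-since-diagnosis group) included. Report the adjusted difference of each active arm from control with its 95% confidence interval. Keep the unadjusted t-test as a supportive analysis.

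The cost is a wording change. All covariates are already collected and N stays at 15 enrolled per arm. The model spends three df on covariates, which pooling the three arms more than replaces (27 error df against 20), at the price of assuming a common variance in the three arms. Fitting the arms pairwise avoids that assumption, but with all three covariates brings no gain at r of about 0.3 or below and a slight loss near r = 0.

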### 2.6. Intervention Groups

In this three-arm RCT, two regimens of nutritional intervention, Bifidobacterium plus perilla oil and Bifidobacterium alone, will be compared to the control group. These two interventions will be completed within 12 weeks of the random allocation of the interventions. We have chosen perilla oil, which is rich in ALA, as an omega-3 supplement based on our observational and other studies. Consumption of a diet rich in ALA facilitates the inhibitory learning of original fear memories more than a diet rich in linolenic acids, one of the n-6 PUFAs, in rats [36]. An ALA-rich chocolate milkshake was recently found to facilitate the inhibitory learning of original fear memories in healthy individuals [37].

Participants in the Bifidobacterium plus perilla oil group will be asked to take 2 capsules (10 billion Bifidobacterium bacteria per capsule) and 1 sachet containing 3 g perilla oil (1.8 g ALA) daily with meals. Perilla oil may be mixed with soup or poured over salad or yogurt. Participants in the Bifidobacterium group will be asked to take 2 capsules (10 billion Bifidobacterium bacteria per capsule) with breakfast. Although there will be no restriction on concomitant drugs/treatments/procedures, information regarding concomitant drugs/therapies during the study will be collected as study data.

To enhance treatment adherence, participants will be contacted by telephone or email at 0, 4, 8, and 12 weeks of the study period. Participants will be informed that if they forget to take a capsule or sachet, they can take a 2-day dose at one time. They will be instructed not to chew the Bifidobacterium capsules. Participants in the intervention groups will be asked to report the number of weeks (0–12) that they have been taking their capsules and sachets during the 12 weeks and the reasons why they did not take them if they took ≤7 (i.e., compliance rate <60%).

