***Assessment***					
Baseline characteristics of participants	CRC		×		
Blood fatty acid test	CRC		×		
Interstitial flora	CRC		×		×
CARS assessed via interview	CRC/masked rater		×(CRC)		×(masked raters)
PHQ-9	PRO questionnaires		×		×
IBS-SI	PRO questionnaires		×		×
Information about allocated groups	CRC			×	
Adverse reactions	CRC/PRO questionnaires				×
				← As needed throughout protocol →	

^1^ Baseline assessment and random allocation for completion within 3 weeks after registration in this study. ^2^ Outcome assessment will be conducted at 12 weeks from random allocation (allowing for a subsequent 14 days).

**Table 2 mps-04-00046-t002:** Data sharing policy for this study. Abbreviation: IPD, individual participant data.

Data Sharing Policy	
Is IPD available?	Yes
What types of data will be shared?	All anonymized IPD reported in the paper (body text, tables, and figures)
Are there any other documents available?	Protocol paper
How long will the data be available for?	For 5 years after publication of the paper
Who will use the data?	Researchers who have presented plans with appropriate methodologies
What types of analysis will this be used for?	For meta-analyses using IPD
How can the data be accessed?	Interested researchers should send a request for data sharing, along with a synopsis of the secondary analysis plan, to the Principal Investigator (RO) by email ([contact]). The study administrative office will examine the request and, if approved, send a letter of approval for data sharing to the requesting researcher.

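### With only baseline and week 12 measured and the baseline score left out of the covariates, the planned mixed model repeats the unadjusted change-score t-test for change, and no stated continuous-outcome analysis adjusts for baseline

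*Protocol article*

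**What the plan says.** Section 2.14 (Statistical Methods) sets out secondary analyses for CARS, PHQ-9, IBS-SI and gut microbiome composition. It says that "differences in the scores at 12 weeks and changes between baseline and 12 weeks will be examined using non-paired t-tests" and, in the same sentence, "mixed-effect models for repeated measures analysis using repeated timepoints and age, disease duration, and hospital as covariates". There are thus two targets, the week-12 difference and the change, and two methods. The same analyses are planned for the two intervention arms combined (n = 30) against control (n = 15).

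Table 1 marks these four outcomes at two points only: the baseline assessment and the outcome assessment. Its footnote reads "Outcome assessment will be conducted at 12 weeks from random allocation". The other contacts do not add outcome data. Section 2.6 says "To enhance treatment adherence, participants will be contacted by telephone or email at 0, 4, 8, and 12 weeks of the study period", and Section 2.12 has adverse reactions asked about at weeks 4 and 8. For CARS, Section 2.5 states "At baseline, the CRC will evaluate the outcome before allocation".

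The primary analysis is an unpaired t-test of week-12 CARS in the per protocol set, without covariates. A secondary analysis covers all randomized participants.

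**The concern.** A repeated-measures model with covariates suggests an adjusted analysis that draws on several visits. Here there is one post-baseline visit. Because the baseline score is not among the covariates, the repeated timepoints can only be baseline and week 12, both in the response. A characteristic that is constant within a participant and enters as a main effect shifts both values equally, so it drops out of the change.

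Two things are at stake. First, this is the only analysis said to adjust for age, disease duration and hospital, and the minimization factors are age and duration from diagnosis. If the model and the change-score t-test agree on change, a reader could take that as robustness to adjustment, when in complete data the two agree by construction. Second, the baseline score, usually the strongest predictor of the week-12 score, is used only by subtraction. In a trial of 15 per arm that aims to estimate an effect size, that may waste precision at no saving in data.

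**Working it through.** **Reproducing the plan's figure.** Section 2.13 gives a difference of 1.0, SD 0.67, one-sided alpha 2.5% and power 90%. Noncentral-t power for an unpaired t-test is 0.884 at 10 per group and 0.914 at 11, so 11 is right; 11 + 4 dropouts = 15, and 15 × 3 = 45. This calculation concerns the primary t-test and does not depend on the mixed model.

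**Algebra for the change.** For a participant in arm a (0 or 1) with covariates x:

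- baseline: y0 = m0 + αa + xβ + e0
- week 12: y1 = m1 + αa + γa + xβ + e1
- change: d = y1 − y0 = (m1 − m0) + γa + (e1 − e0)

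The term xβ is gone. Let k = Cov(e0, e1 − e0) / Var(e1 − e0). The remaining information is in y0 − kd, which is uncorrelated with d and has arm coefficient α − kγ. Because α is free, it absorbs kγ, and this part says nothing about γ. With complete pairs, γ is therefore the raw difference in mean change, whatever the covariates and whatever the 2 × 2 covariance.

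**Numerical check.** 60 simulated two-arm trials were run, half 15 v 15 and half 30 v 15, with effect −1.0 and SD 0.67. Assumed: baseline to week-12 correlation 0.5 and covariate effects of 0.3 to 0.4 points. The fit was REML with unstructured covariance.

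| Quantity | Result |
|---|---|
| Arm-by-time estimate minus difference in mean change, complete data | at most 2e-14 |
| Difference in t statistics, complete data | at most 3e-7 |
| One random-intercept fit against the t-test | −0.96267 both, t = −4.977 both |
| Shift in the change estimate if covariate-by-time terms are added | mean 0.05, max 0.29 |
| Week-12 contrast of the model against the raw difference | moves 0.09 on average, max 0.27 |
| Mean SE of the week-12 contrast, without and with covariates | 0.243, 0.230 |
| 4 of 15 per arm missing week 12: arm-by-time against completers' change difference | mean 0.05, max 0.19 |
| Same missingness: effect of adding the covariates on arm-by-time | mean 0.02, max 0.07 |
| Mean SE: arm-by-time, then common-baseline model (covariates as main effects) | 0.222, 0.190 |

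**Week-12 contrast.** This is α + γ. The covariates adjust it, but the arm difference at baseline is fitted freely. Without covariates and with complete data it is simply the raw week-12 mean difference, so the baseline score does nothing to correct for chance imbalance.

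**What baseline adjustment would gain.** Let s0 and s1 be the SDs at baseline and week 12 and ρ their correlation. The documents give no ρ and no separate week-12 SD, so both are assumed.

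- Change-score variance is proportional to s0² + s1² − 2ρs0s1.
- Baseline-adjusted variance is proportional to s1²(1 − ρ²).
- With s0 = s1 the ratio is 2(1 − ρ)/(1 − ρ²) = 2/(1 + ρ): 2/1.3 = 1.54, 2/1.5 = 1.33, 2/1.7 = 1.18.
- With s0 = 0.67 and s1 = 1.0 the numerator is 1.4489 − 1.34ρ: 1.0469/0.91 = 1.15, 0.7789/0.75 = 1.04, 0.5109/0.51 = 1.00.

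**The case against.** The strongest reply is that the sentence does not fix the model. It names timepoints and covariates but not the interaction terms, any baseline constraint or the contrast to be reported. The article condenses a longer protocol, and such terms commonly sit there or in a statistical analysis plan. A constrained model with covariate-by-time terms would be compatible with the quoted words. This stands to the extent that the point depends on the literal reading. It does not dispose of the point, because the article does fix the covariate list and the visit schedule, and the baseline score is missing from the list.

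Two stronger readings are tempting, and the documents do not support either.

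- A reader might infer that the covariates adjust nothing. Section 2.14 also names the week-12 difference, and the model's contrast there is adjusted. In the all-randomized set with missing week-12 scores, the covariates also move the change estimate slightly.
- A reader might infer that the model would report half the true effect. That needs an arm main effect without interaction and equal variances at the two visits. With SDs of 0.67 and 1.0 and correlation 0.5 (assumed), the week-12 weight in such a term is 0.15, not 0.50. The plan nowhere says that an arm effect averaged over both visits will be reported.

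It is also fair to say that these are secondary analyses in an exploratory trial, and that the precision gain could be negligible. Entry requires at least 3 on the CARS intensity item, which plausibly narrows the baseline spread relative to week 12, and the less favourable ratios above would then be the relevant ones.

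**Conclusion.** The point holds in limited form. Under the literal reading, the mixed model gives no covariate-adjusted effect on change in participants with both measurements; it reproduces the planned change-score comparison. For CARS in the per protocol set, week-12 completeness is part of the definition, so the identity is exact there wherever baseline is recorded. In the all-randomized set it is approximate. Its week-12 contrast is adjusted for age, disease duration and hospital, but not for baseline. No stated continuous-outcome analysis adjusts for baseline other than by subtraction.

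The cost in precision runs from none to a variance about 1.5 times larger than necessary for the change score, depending on a correlation and a variance ratio that the documents do not give. Nothing here biases the primary analysis or alters the sample size.

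**What to change.** For each continuous secondary outcome, including the secondary CARS analysis, name the arm difference at week 12 as the reported effect and state one of these models:

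- **All-randomized set:** a mixed model of the baseline and week-12 values, with baseline means constrained to be equal across arms and age, disease duration and hospital each entered with its interaction with time.
- **Participants with week-12 data:** an ANCOVA of the week-12 value on arm, baseline value, age, disease duration and hospital.

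The cost is a sentence in the plan and a changed model statement, with no new data. There is some statistical cost. With 11 per arm in a two-arm comparison, the t-test has 22 − 2 = 20 degrees of freedom and the ANCOVA 22 − 6 = 16, if each covariate takes one. The ANCOVA also drops participants without a week-12 value, so the constrained mixed model suits the all-randomized set better. If the change-score t-test is kept, the report should not offer its agreement with an unconstrained, main-effects mixed model as evidence of robustness to covariates.
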